## Abstract

The aim of this multi-country, cluster-randomized trial is to test the impact of pharmacy-based health promotion to reduce the blood pressure of individuals with hypertension over a 12-month period in Bangladesh and Pakistan. The trial will be implemented with two arms. In Bangladesh, the estimated sample size is around 3600 hypertensive patients. In Pakistan, we will select samples equivalent to 10% of the participants from Bangladesh, comprising 360 hypertensive patients from four pharmacies. Community pharmacies will be randomized into one of two parallel groups (allocation ratio 1:1). Pharmacy professionals in the treatment arm will provide their patients with educational training and counseling, as well as phone calls/mobile text messages and care coordination in the health sector, as part of the intervention. The study will be conducted in three phases: a baseline survey with intervention, a midline survey with intervention and follow-up, and an endline survey with impact evaluation. The primary outcome of the study will be BP. The secondary outcomes will be BP controlled to target, treatment adherence, quality of life, mortality or hospital admission rates resulting from hypertension and its related complications, incremental cost per health-related quality of life gained, knowledge on healthy lifestyle and dietary behavior, and change in the prevalence of current smoking status.

## 1. Introduction

Globally, hypertension is a leading cause of cardiovascular disease and death [1]. Approximately two-thirds of the world’s 1.28 billion hypertensive patients live in low- and middle-income countries (LMICs) [2]. South Asian countries have experienced a steep rise in hypertension prevalence, with Bangladesh, India, and Pakistan having 48.0%, 52.3%, and 46.2% [3,4,5]. Hypertension in low-income countries is disproportionately caused by rapid urbanization, unhealthy lifestyles, and inactivity [6,7]. In LMICs, awareness, treatment, and control of hypertension remain unacceptably low, mostly because of poor medication adherence, limited health resources, and difficulties accessing healthcare [8,9]. Furthermore, a systematic review suggested that factors such as inadequate healthcare information, dissatisfaction with the services provided, and fewer interactions with physicians contribute significantly to medication nonadherence [10]. LMICs with weak health literacy, poor health systems, and high cardiovascular disease fatality rates have a disproportionately high prevalence of hypertension [11,12]. Consequently, most hypertensive patients take medications only when symptomatic and lead sedentary lifestyles despite being aware of dietary recommendations [13,14].

The American Heart Association (AHA) and World Health Organization (WHO) have set specific blood pressure targets to reduce the risk of cardiovascular events [2,15]. The AHA defines Stage 2 hypertension as having a systolic blood pressure (SBP) of 140 mmHg or higher or a diastolic blood pressure (DBP) of 90 mmHg or higher, indicating that these levels are significant thresholds for initiating treatment to prevent complications [15]. Lifestyle and medication adherence can be improved by educating the patients [15,16,17,18,19]. Using the available non-physician health workforce in LMICs is a logical step for hypertension management, where doctors are often scarce. The approach could be cost-effective and essential for resource-constrained countries like Bangladesh, India, and Pakistan. In addition to many non-physician healthcare providers (HCPs), community pharmacists (CPs) are widely recognized as valuable sources of reliable information for people of all ages [19,20]. Pharmacies can be the first contact points for patients seeking primary healthcare services, due to their relatively convenient community location. They also assist hypertensive patients in achieving their treatment goals with individualized advice and education, increasing patients’ knowledge for better management of hypertension [21]. The results of a meta-analysis showed that CPs successfully reduced systolic blood pressure (SBP) and diastolic blood pressure (DBP) by 9.3 mmHg and 3.6 mmHg, respectively, over a one-year period [17].

As of today, only a small number of studies in Pakistan and India have demonstrated the above findings, including improved control of blood pressure, medication adherence, and understanding of hypertension [22,23,24,25,26]. To our knowledge, no study has examined this unique intervention’s cost-effectiveness and impact on mortality and hospital admission rates in Bangladesh and Pakistan. This information is crucial to informing policymakers on the potential of CP as an efficient and high-quality care solution compared to physician-centered care. Due to their similarities and differences in culture, religion, socioeconomic background, and other aspects, the findings of this study will be adaptable, transferable, and scalable to different settings or other LMICs, preventing numerous premature deaths, strokes, and heart attacks every year.

## 2. Aim and Hypothesis

In this study, we will test the effectiveness and cost-effectiveness of enhanced pharmacy-based care provided to community people in Bangladesh and Pakistan on blood pressure control and treatment adherence. This is the first multi-country trial to evaluate pharmacy-based health promotion in these two countries, focusing on the role of CP in hypertension treatment.

### 2.1. Hypothesis

The study hypothesizes that hypertensive patients receiving the community pharmacy-based health intervention will achieve the following outcomes:Reduced systolic and/or diastolic BP;Improved treatment adherence and BP control to target levels;Reduced hospitalization and death due to cardiovascular events;Positive changes in lifestyle behaviors;Increased in HRQoL.

### 2.2. Objectives

This study evaluates the effectiveness of community pharmacy-based interventions in controlling BP among hypertensive patients in Bangladesh and Pakistan. The study assesses both clinical outcomes and cost-effectiveness. The primary objective is to evaluate the impact of patient counseling and education by CPs on BP control and treatment adherence, followed by a cost-effectiveness analysis to demonstrate the value for money in public spending on hypertensive care. Specifically, the cost-effectiveness analysis will calculate the cost per unit (mmHg) of blood pressure reduction and the cost per HRQoL gained.

## 3. Methods

### 3.1. Study Design and Settings

A two-arm parallel-group cluster-randomized controlled trial (cRCT) will be conducted among hypertensive patients in Bangladesh and Pakistan. In the first stage, two districts in Bangladesh were chosen randomly: Rangpur district and Chuadanga district. In the second stage, from each district, one subdistrict was selected randomly: Pirganj and Alamdanga. Finally, 20 pharmacies were chosen from each subdistrict to reach our target sample. The overall flow of the study is shown in Figure 1. Randomization clusters are community pharmacies. Each country will follow a two-arm cRCT design. According to a 4.65% BP reduction with a standard deviation of 49.78 [27], the estimated sample size for Bangladesh is around 3600 at 80% power and 5% significance. Approximately 10% of participants will be selected based on a Bangladesh sample from Pakistan (360 hypertensive patients from four pharmacies). The average number of hypertensive patients per pharmacy is 90. Due to financial limitations and logistical challenges, it is necessary to choose 10% of the participants from Pakistan. This decision was primarily influenced by the availability of resources and the specific focus of our research project. These limitations included budget constraints that impacted the scope of the study and logistical challenges related to the larger geographic and infrastructural differences between the two countries. Conducting a full-scale study in Pakistan similar to Bangladesh is not feasible with the available resources. However, by including participants from Pakistan, we aim to enhance the diversity within our study population, despite some similarities in sociodemographic profiles and health behaviors between the two countries.

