### 3.8. Outcome Evaluation

The primary effectiveness of the outcome will be evaluated by changes in the SBP and DBP of the patients from baseline to final follow-up at 12 months post-intervention. The secondary outcome measures will include (1) BP controlled to target (SBP < 140 mmHg and DBP < 90 mmHg); (2) composite outcome of death (all-cause) or hospital admission due to CHD, heart failure, or stroke; (3) incremental cost per HRQoL gained from baseline to end of follow-up; (4) improvement in the knowledge of patients on healthy lifestyle; (5) change in dietary salt intake; (6) change in quality of life; (7) change in the prevalence of current smokers; and (8) the treatment adherence rate. Hypertensive patients with poor adherence to their treatment regimens experience uncontrolled blood pressure. Adherence to hypertension treatment is defined as following the treatment regimen agreed to with their physician. According to the previous literature [29,30,31], a reduction of 5 mmHg of SBP is considered clinically relevant as it has been found to be significantly associated with a risk reduction in CHD, stroke, and other serious cardiovascular events. Health service utilization parameters will include the number and reason for visits to physicians and hospital admission, and when further complicated, the death of the patient. The cost-effectiveness measures are incremental cost per mmHg BP reduction or cost per HRQoL gained from baseline to end of follow-up at 12 months. For determining dietary salt intake level, a 24 h urinary sodium measurement will be opted.

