## 5. Limitations

The main limitation could be the high dropout rate as patients may be too busy to attend an educational session, some might lose interest and discontinue during the study period, and some participants might miss their routine follow-up visits due to political unrest or any other unavoidable circumstance. Although the patients’ presence can never be guaranteed, the research team and the CP will try their best to contact and persuade patients to participate. Secondly, missing data can be an issue in this trial; however, the planned analyses will follow intent-to-treat methods to minimize bias from dropout over time. A repeated-measurement bias can also be expected as the same questionnaire will be used at both baseline and endline surveys. Finally, due to the short follow-up duration, the long-term benefits of this CP model may not be observed at length. Despite these limitations, the study findings can give a basis for improving the future care of hypertensive patients in primary healthcare facilities in South Asia.

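### The Bangladesh sample size of 3600 allows for neither clustering nor dropout and is not on the mmHg scale, so the stated 80% power fails on its own inputs and is unsupported for the primary outcome

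*Protocol article*

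**What the plan says.** Section 3.1 of the protocol article gives the only power statement: "According to a 4.65% BP reduction with a standard deviation of 49.78 [27], the estimated sample size for Bangladesh is around 3600", set "at 80% power and 5% significance". The SD has no unit. The text does not say whether the 4.65% is absolute or relative, or whether it refers to SBP or DBP.

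The same section says "Randomization clusters are community pharmacies". It takes 20 pharmacies from each of two subdistricts, with an average of 90 patients per pharmacy. That makes 40 clusters and 40 x 90 = 3600 patients. Section 3.3 allocates pharmacies 1:1 and repeats the figure of 90.

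Section 3.8 makes the primary outcome the change in SBP and DBP from baseline to 12 months, and adds that "a reduction of 5 mmHg of SBP is considered clinically relevant". Section 3.13 plans two-tailed tests at 0.05 and mixed models with pharmacy as a random effect. Section 5 says "The main limitation could be the high dropout rate". The article gives no ICC, design effect or dropout rate.

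**The concern.** Patients of one pharmacy share a pharmacist, a catchment area and, in the intervention arm, the same counselling, so their outcomes are likely to be correlated. A sample size that treats 3600 patients as independent overstates the information in 40 pharmacies. Patients lost before 12 months reduce it further. The effect and SD are also on a different scale from the outcome that the trial will test.

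At stake is the meaning of the 80%. If it fails on its own inputs and does not refer to the primary outcome, the article contains no valid power statement for that outcome, and a null result could not be judged against the claimed 80%.

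**Working it through.** **1. Reproducing the 3600.** Inputs from section 3.1: difference 4.65, SD 49.78, power 80%, alpha 5%. The tests are two-sided (section 3.13) and allocation is 1:1 (section 3.3).

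n per arm = 2 x (1.96 + 0.8416)^2 x (49.78/4.65)^2 = 2 x 7.849 x 114.605 = 1799

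Two arms give 3598. The t-based version gives 1800 per arm, hence 3600. Variants do not fit: a one-sided test gives 2836 and 90% power gives 4818. The published inputs account for every patient, so the design effect used is 1 and the dropout allowance is 0.

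**2. Adding the clustering.** With 90 patients per pharmacy, DE = 1 + 89 x ICC. The article gives no ICC, so the values below are assumed.

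Power = Phi(4.65 / SE - 1.96), SE = 49.78 x sqrt(2 x DE / 1800); detectable difference at 80% power = 2.8016 x SE.

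| ICC (assumed) | DE | Power | Detectable difference |
|---|---|---|---|
| 0 | 1.00 | 80% | 4.65 |
| 0.001 | 1.09 | 77% | 4.85 |
| 0.01 | 1.89 | 53% | 6.4 |
| 0.02 | 2.78 | 39% | 7.75 |
| 0.03 | 3.67 | 31% | 8.9 |
| 0.05 | 5.45 | 22% | 10.9 |

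The normal approximation is generous with 40 clusters. A t-test on 40 - 2 = 38 degrees of freedom gives 78% even at ICC 0.

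**3. Dropout alone.** With an assumed 20% loss and no clustering, 1440 per arm remain. SE = 49.78 x sqrt(2/1440) = 1.855, so power = Phi(4.65/1.855 - 1.96) = 71%.

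**4. The scale of the inputs.** A yes/no outcome has an SD of 100 x sqrt(p(1 - p)) in percentage points. Setting this to 49.78 gives p = 0.453 or 0.547. A 4.65-point difference centred on 0.453 needs 3596 patients by the two-proportion formula. The pair thus behaves like a difference between proportions. That is an inference from a numerical match, because the source cited for the figures is not at hand.

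**5. Power for the mmHg outcome.** The article gives no mmHg SD and no ICC, so this power cannot be computed from it. As illustration, take 5 mmHg SBP (section 3.8), 40 pharmacies and an assumed 20% dropout. Then m = 72, n = 1440 per arm and DE = 1 + 71 x ICC. Power comes from a noncentral t with 38 df and noncentrality 5 / [SD x sqrt(2 x DE / 1440)].

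| SD, mmHg (assumed) | ICC (assumed) | DE | Noncentrality | Power |
|---|---|---|---|---|
| 20 | 0.03 | 3.13 | 3.79 | 96% |
| 20 | 0.05 | 4.55 | 3.14 | 87% |
| 25 | 0.03 | 3.13 | 3.03 | 84% |
| 25 | 0.05 | 4.55 | 2.52 | 69% |

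Without dropout (normal approximation), 3600 patients in 40 pharmacies keep 80% power for 5 mmHg up to an ICC of about 0.13 (SD 15), 0.07 (SD 20) or 0.04 (SD 25).

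**The case against.** The best defence is that the trial may well be large enough. The inputs in section 3.1 amount to a standardised effect of 4.65/49.78 = 0.093, far smaller than 5 mmHg against an SD of 20 (0.25). Most of the illustrative mmHg figures stay above 80% after clustering and dropout. This stands. A reader might infer from the 53% or 22% that the trial is underpowered for its primary outcome, and the document does not support that. Those figures belong to the 4.65/49.78 effect, and the mmHg power turns on an SD and an ICC that the article does not give.

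A reader might also take it as settled that the calculation was made for a binary outcome. The match in step 4 is close, but section 3.1 speaks of a BP reduction and the source cannot be checked. Section 2.2 states the primary objective as BP control and treatment adherence, so a proportion would not be foreign to the trial. That may explain the inputs. It does not remove the mismatch with the primary outcome in section 3.8, and it does not answer the clustering point.

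A third defence is that section 3.13 handles clustering in the analysis, with cluster-adjusted confidence intervals. True: the defect lies in the planning justification, not in the planned model. But that model will carry the between-pharmacy variance that the sample size left out.

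Finally, an article condenses a fuller protocol, and an ICC could have been cut. That does not help here, because the published inputs already yield the whole 3600 and leave no room for an unstated inflation.

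**Conclusion.** The power statement is wrong as written. The 3600 comes from a formula for individual randomisation, with a design effect of 1 and no dropout margin, in a trial of 40 randomised pharmacies. On its own inputs the 80% is false for any ICC above 0. Over assumed ICCs of 0.01 to 0.05 power is 53% to 22%, and the detectable difference is 6.4 to 10.9 instead of 4.65. That conclusion does not depend on a particular ICC; only its size does.

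For the primary outcome in mmHg the 80% is unsupported. It may be exceeded or missed: the illustrations run from 96% to 69%, all resting on assumed SDs, ICCs and 20% dropout. That the inputs describe a proportion remains an inference.

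**What to change.** Rewrite the sample size paragraph of section 3.1 at the planned 40 pharmacies of 90:

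- Base it on 12-month change in SBP, with the 5 mmHg of section 3.8, and also on DBP, since both are named as primary. Give a sourced SD in mmHg for each.
- Apply 1 + (m - 1) x ICC with a sourced ICC and a range around it. Take m after expected dropout and use 38 degrees of freedom.
- State the resulting power or detectable difference, whatever it is.
- If the 4.65/49.78 calculation is kept, say which outcome it is for, and replace its 80% by the cluster-adjusted power or detectable difference.

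The rewrite costs one paragraph and a search for an SD and an ICC. It does not in itself require more patients. If the sourced inputs lie near the unfavourable end, the sponsor would have to accept a larger detectable difference or add pharmacies. The power stated for the 4.65 effect will become less favourable.

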### 3.2. Study Participants

As part of the consensus, participants who come to the pharmacy to purchase hypertensive medication will be listed with their basic information. The following information will be needed: their name, address, gender, duration of hypertension, who will be taking the medication, and at least two contact numbers. In order to confirm whether prospective hypertensive adults are hypertensive, their blood pressure will be measured again. Both male and female participants will be invited to participate. The eligibility criteria include (1) aged 18 years and above; (2) hypertensive (defined as (a) SBP ≥ 140 mmHg and DBP ≥ 90 mmHg and/or taking antihypertensive medications); (3) capable of communicating verbally in local language; (4) permanent resident of the study area; (5) access to mobile phone; and (6) consent to participate. Exclusion criteria are (1) pregnant and lactating women; (2) individuals with advanced medical disease (e.g., cancer, heart failure, chronic obstructive pulmonary disease, end-stage renal disease, advanced neurological disease, etc.); (3) those having cognitive and psychiatric problems; (4) involvement in any other interventional study; and (5) individuals who are unable to give informed consent. Pharmacists’ inclusion criteria include (1) ensuring a sufficient amount of time to implement intervention on hypertensive patients; (2) consent to participate; and (3) being able to operate a smartphone or tablet. Screening for patients’ eligibility will be conducted by the CP during regular visits, and upon deeming them eligible, the CP will inform the principal investigator or research assistant of this study to approach the patients, briefly explain the study, and ask them to sign informed consent.

### 3.3. Randomization

Community pharmacies will then be randomized to one of two parallel groups (allocation ratio 1:1) using a computer-generated random number sequence. Participants and pharmacies will be assigned to intervention and control groups in a 1:1 ratio. To reach the target sample, every pharmacy needs to recruit 90 hypotensive patients. The randomization and study procedure are presented in Figure 1.

### 3.4. Blinding

Only the outcome evaluators will be blinded to group allocation due to the nature of the intervention. To prevent contamination, we will select the CPs of the treated group and control from considerably different locations. CP will deliver the intervention, and research assistants (field enumerators and supervisors) will engage in data collection from the participants. However, pharmacists and research assistants will not be blinded since they are involved in interventional processes.

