### 3.5. Training of the Pharmacists

Mandatory communication training will enhance treatment integrity since pharmacist skills and competences will determine the quality of the intervention. Before the study begins, CPs in the intervention arm will receive training involving both theoretical and practical sessions. It will cover the prevalence, risk factors, complications, and diagnosis of hypertension, as well as non-pharmacological ways of preventing it. On the practical side, CPs will learn how to measure blood pressure using a manual sphygmomanometer, interpret the measurements, and educate and counsel hypertensive patients through audio–visual presentations. As part of the intervention strategy, blood pressure control, the identification of hypertension-related complications, health education, medication and lifestyle modification counseling, follow-up, and referral to a medical practitioner or hospital will be provided.

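### Selecting treated and control pharmacies from different locations (3.4) cannot stand beside random allocation of individual pharmacies (3.1, 3.3); if followed, it ties arm to place

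*Protocol article*

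**What the plan says.** Section 3.1 states that "Randomization clusters are community pharmacies". For Bangladesh, two districts were drawn, then "from each district, one subdistrict was selected randomly: Pirganj and Alamdanga", and then "20 pharmacies were chosen from each subdistrict to reach our target sample". Pakistan contributes four pharmacies. Section 3.3 gives the mechanism: "Community pharmacies will then be randomized to one of two parallel groups (allocation ratio 1:1) using a computer-generated random number sequence".

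Section 3.4, on blinding, adds a measure against contamination: "we will select the CPs of the treated group and control from considerably different locations".

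Section 3.13 treats the pharmacy as a random effect in a mixed model that compares changes across time points. Section 3.8 defines the primary outcome as change in SBP and DBP from baseline to 12 months.

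On timing, Section 3.5 says "Before the study begins, CPs in the intervention arm will receive training", and Section 3.2 says of screening that "eligibility will be conducted by the CP during regular visits". Table 2 puts selection and consent in weeks 1 to 4, randomisation and allocation in week 5, and the baseline assessment at Month 0.

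**The concern.** The sentence in Section 3.4 is a positive statement about how the two arms come to consist of the pharmacies they do. It makes the choice of a pharmacy depend on both its arm and its place. A random sequence over individual pharmacies leaves no room for that choice.

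A field team that carried out Section 3.4 literally would override the sequence. The comparison between arms would then also be a comparison between places. Anything that moves BP differently in those places over the year, such as a change in medicine supply or in access to doctors, would enter the estimated effect. More patients or more pharmacies in the same places would not average it out, and no analysis plan could reliably undo it after recruitment.

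**Working it through.** **The plan's own figures.** Section 3.1 gives an effect of 4.65, an SD of 49.78, 80% power and 5% significance; Section 3.13 makes tests two-sided. Per arm, n = 2 × (1.960 + 0.842)² × (49.78 / 4.65)², which rounds up to 1,800, or 3,600 in total. This matches the plan. So do 40 pharmacies × 90 = 3,600 and 4 × 90 = 360. The sample size neither supports nor weakens the present point.

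**The two rules side by side.**

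| Rule | What decides a pharmacy's arm | Can the other rule hold? |
|---|---|---|
| 3.1 and 3.3 | Computer sequence over individual pharmacies | No. Treated and control pharmacies fall where the sequence puts them |
| 3.4, read literally | Location | No. A pharmacy's place fixes or restricts its arm |

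The sequence would not itself produce a separation by place. If 20 of the 40 Bangladeshi pharmacies were drawn freely, the chance that the arms would split exactly along the two subdistricts is 2 / C(40,20) = 1.5 × 10⁻¹¹. A systematic separation would have to come from selection.

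**Why the random effect does not help.** Write the mean change in pharmacy j as μ + τ × arm + γ(location) + u(j) + error, where u(j) is the pharmacy effect. If location determines arm, the contrast between arms estimates τ + [γ(treated locations) − γ(control locations)]. The model takes u(j) to be independent of arm, so it allows for scatter among pharmacies but not for a shift that all pharmacies in one arm share. If no location contained both arms, even a location term could not separate γ from τ. It can do so only where both arms occur within each location.

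**What γ is made of.** The outcome is a change from baseline, so a stable difference in BP level between places largely cancels. What remains is a difference in trend over 12 months. If baseline levels differ between arms, regression to the mean adds to it, because the transient part of a high baseline falls back without treatment.

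**Illustration only.** The documents give no location difference. Assume a difference b in change between the arms' locations, with no true effect. Take the standard error implied by the plan's sample size, 49.78 × √(2/1,800) = 1.66. The two-sided 5% test then rejects with these probabilities:

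| b | 0 | 1 | 2 | 3 | 4.65 |
|---|---|---|---|---|---|
| Rejects | 5% | 9% | 23% | 44% | 80% |

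Here b is in the units of the plan's planned effect, which Section 3.1 states as a percentage, so it cannot be read as mmHg. This standard error ignores clustering. With a design effect of 1 + 89 × ICC and an assumed ICC of 0.01, 0.02 or 0.05, the figure at b = 4.65 falls from 80% to 53%, 39% or 22%. The table shows the direction of the problem, not its size.

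**The case against.** The best defence is that the sentence is loose wording for something sound: pharmacies are first chosen far enough apart that treated and control sites are not neighbours, and are then randomised. That would keep the randomisation valid, and the stated purpose fits it. The text does not say this, however. It speaks of selecting the pharmacies of each arm from different places. Figure 1, which is said to present the randomisation, is not shown here, so it cannot settle the matter. If spacing was meant, the correction is a short rewording, but it is still needed.

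Three stronger readings are tempting and are not supported:

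- A reader might infer that one subdistrict goes to each arm, since Bangladesh has only two. No section assigns a subdistrict to an arm. That is the extreme case of the rule, not a stated design.
- A reader might want to quote a definite false-positive rate. Any such rate rests on assumed variances between areas and between pharmacies. A calculation on BP levels would also use the wrong quantity, because the primary outcome is change from baseline.
- A reader might infer that pharmacists screen patients already knowing their arm, since Section 3.5 trains the intervention arm before the study starts and Section 3.2 has pharmacists do the screening. Table 2 puts selection and consent before randomisation, and training fits between week 5 and Month 0. Selection bias at screening is therefore a possible reading of imprecise wording, not an established feature of the plan.

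**Conclusion.** The contradiction between Section 3.4 and Sections 3.1 and 3.3 stands and should be resolved, because it bears on whether the pharmacies are validly randomised. If location decides the arm, arm and place are confounded and the pharmacy random effect does not repair it. This conclusion rests on the wording alone and needs no assumed figure.

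The size of the resulting bias is unknown. It depends on how far the arms would actually be separated by place and on how much BP trends differ between those places. The documents give neither.

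The timing of pharmacist training is a secondary point of wording. It matters only if enrolment counts as part of the study that training is to precede.

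**What to change.** - Delete the sentence in Section 3.4 that selects arms by location.
- Deal with contamination before allocation: set a minimum spacing between any two pharmacies, whatever arm they may later receive, as far as the pharmacies already chosen allow.
- Randomise 1:1 within strata: 10:10 in Pirganj, 10:10 in Alamdanga and 2:2 in Pakistan. This gives 22 pharmacies per arm and keeps the planned 44.
- Include the stratum in the Section 3.13 model.
- Reword Section 3.5 to agree with Table 2: arms are revealed and intervention pharmacists trained only after screening and consent have closed (weeks 1 to 4) and randomisation is done (week 5), and before Month 0.
- If pharmacies have already been allocated, state which rule was followed.

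The cost is a few sentences, a stratified allocation list and two stratum terms in the model. The practical downside is some constraint on which pharmacies can be used. Section 3.1 reports the Bangladeshi pharmacies as already chosen, so a few that lie too close together may need replacing.

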Additional data will be collected by enumerators to enable the calculation of the QRisk2 score, including the following:Blood pressure (lowest of two measurements used);Fasting blood glucose level;Weight and height;Smoking status (options aligned with QRisk2).

For the economic evaluation, all costs related to pharmacy-based intervention will be collected including patient counseling and education time and training, telephone and material costs, cost of care at the hospital (for complicated cases requiring visits to physicians and admission), and other administrative costs.

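### The article says outcome evaluators are blinded, but every person it describes as taking blood pressure, the primary outcome, is unblinded

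*Protocol article*

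**What the plan says.** Section 3.4 (Blinding) makes three statements in one paragraph:

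- "Only the outcome evaluators will be blinded to group allocation due to the nature of the intervention". The term *outcome evaluators* is not defined there or elsewhere.
- "research assistants (field enumerators and supervisors) will engage in data collection from the participants".
- "pharmacists and research assistants will not be blinded since they are involved in interventional processes".

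Section 3.7 (Data Collection) then states: "Additional data will be collected by enumerators to enable the calculation of the QRisk2 score". The first item in that list reads "Blood pressure (lowest of two measurements used".

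Section 3.8 (Outcome Evaluation) defines the primary outcome as "changes in the SBP and DBP of the patients from baseline to final follow-up at 12 months post-intervention". The first secondary outcome is BP controlled to target, a threshold on SBP and DBP. Table 2 schedules BP in both arms at months 0, 6 and 12 and does not name the person who takes it.

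The only other people described as measuring BP are the pharmacists. In section 3.5, "CPs will learn how to measure blood pressure using a manual sphygmomanometer". Section 3.6 has BP checked at each intervention session, which the pharmacist delivers. Section 3.4 declares the pharmacists unblinded as well.

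**The concern.** The article relies on blinded outcome assessment because neither pharmacists nor patients can be blinded to counselling. That protection works only if the person who takes the reading does not know the arm. Here the staff who collect the data are declared unblinded, and the reason given is their part in the intervention.

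A reading taken by someone who knows both the arm and the hypothesis can drift in one direction in one arm. That drift adds directly to the estimated arm difference. Neither intention-to-treat analysis nor a mixed model with pharmacy as a random effect removes it, and it cannot be repaired once the readings have been taken.

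The reading rule is a smaller matter. Keeping the lower of two readings lets one value decide the record, which gives an unblinded observer more room to influence it. It also makes BP control look better than it is in both arms.

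**Working it through.** **1. Roles side by side (protocol article)**

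| Role | Takes BP? | Blinded? |
|---|---|---|
| Field enumerators (research assistants) | Yes, section 3.7 | No, section 3.4 |
| Supervisors (research assistants) | Collect data, section 3.4; monitor the intervention, section 3.7 | No, section 3.4 |
| Pharmacists | Yes, in sessions, sections 3.5 and 3.6 | No, section 3.4 |
| Outcome evaluators | Not described | Yes, section 3.4 |

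The only blinded role has no described task, and every role described as taking BP is unblinded.

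**2. The plan's own figure**

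The inputs in section 3.1 are a difference of 4.65 (written as a percentage), SD 49.78, 80% power and 5% significance. Tests are two-tailed (section 3.13).

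n per arm = 2 × (1.96 + 0.84)² × 49.78² / 4.65² ≈ 1800, so 3600 in total. The stated size is reproduced. It also equals 40 pharmacies × 90 patients, or 1800 per arm. This figure has no bearing on blinding; it only supplies the n used below.

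**3. Illustration: how often a pure reading bias would look like an effect**

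Assume no true effect and a between-arm reading bias b.

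- Design effect: DE = 1 + (90 − 1) × ICC
- SE = SD × √(2 × DE / 1800)
- P(significant) = 1 − Φ(1.96 − b/SE) + Φ(−1.96 − b/SE)

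The ICC, the SD of 20 mmHg and b = 2 mmHg are assumptions. The article's SD of 49.78 is read as mmHg.

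| SD | ICC | DE | SE (mmHg) | P(significant), b = 2 mmHg |
|---|---|---|---|---|
| 20 | 0.01 | 1.89 | 0.92 | 59% |
| 20 | 0.02 | 2.78 | 1.11 | 44% |
| 20 | 0.05 | 5.45 | 1.56 | 25% |
| 49.78 | 0.01 | 1.89 | 2.28 | 14% |
| 49.78 | 0.02 | 2.78 | 2.77 | 11% |
| 49.78 | 0.05 | 5.45 | 3.87 | 8% |

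The nominal rate is 5%. The bias used is less than half of the 5 mmHg that section 3.8 calls clinically relevant.

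**4. Lowest of two readings (secondary)**

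With within-visit SD SDw, the expected lower reading lies SDw/√π below the true level. That is 2.8 mmHg at SDw 5 and 4.5 mmHg at SDw 8 (both SDw values assumed). Applied equally in both arms, this shift cancels in the mean arm difference.

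Its within-visit variance is 0.682 × SDw², against 0.5 × SDw² for the mean of the same two readings. The excess of 0.182 × SDw² is about 1% (SDw 5) to 3% (SDw 8) of a total variance of 20² = 400.

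The effect on BP control was simulated with 1,000,000 patients per setting. The assumptions were true mean 142/86 mmHg, SD 18/10, SDw 5 to 8 for SBP and 3 to 8 for DBP, SBP–DBP correlation 0 to 0.7, and the lowest SBP and lowest DBP each kept. The control rate is about 6 to 13 points higher than with the mean of two. For example, at correlation 0.6 and SDw 5 for both, it rises from 38% to 45%.

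**The case against.** The strongest reply is that a journal article condenses the protocol. A separate blinded assessor, or blinded analysts, may be what is meant by outcome evaluators, with details in the operational manual mentioned in section 3.7. Silence alone would be no finding. But the article is not silent: it assigns data collection, assigns BP to enumerators and declares those staff unblinded. If the term means analysts, blinding them does not protect a reading already taken by someone who knew the arm. The contradiction stands.

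Other objections do limit the point:

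- **Lowest-of-two and the primary outcome.** A reader might infer that the primary outcome is scored this way. The rule appears only in the QRisk2 list; section 3.8 and Table 2 give no reading rule. It is the only rule in the article, so its use for the primary outcome is an inference.
- **Lowest-of-two as a source of treatment-effect bias.** A reader might add the 2.8 to 4.5 mmHg shift to the observer bias. That is not supported: the shift cancels in the mean arm difference if the rule is applied equally.
- **Size.** A single figure such as 44% (SD 20, ICC 0.02) could be taken as the trial's error rate. It is one assumed point, and the result falls to about 11% at the article's own SD with the same ICC.
- **Device.** The manual sphygmomanometer is named only in pharmacist training. The article does not state what the enumerators use, so how far their readings depend on the observer is not known.

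**Conclusion.** The contradiction within section 3.4, and between it and sections 3.7 and 3.8, is firm and needs no assumption: the article claims blinded outcome evaluation, but describes no blinded person taking the primary outcome. Followed as written, the primary outcome lacks the protection claimed.

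The size of the consequence is conditional. It depends on an assumed between-arm bias, SD and ICC, as tabulated above. The article does not show that a bias will occur or how large it would be, and a reader should not infer that it does.

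The reading rule is a secondary matter. If lowest-of-two is used for study BP, it overstates the absolute control rate in both arms, adds slight noise and gives an unblinded observer more leverage.

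**What to change.** 1. Reconcile sections 3.4, 3.7 and 3.8 by naming who takes BP at months 6 and 12 and whether that person is blinded.
2. Keep those enumerators out of all intervention activity, which the pharmacists already deliver. Do not tell them the arm, and have them take BP before any question that would reveal counselling.
3. Leave monitoring of delivery to supervisors who take no BP.
4. If this cannot be done, withdraw the statement that outcome evaluators are blinded and report BP assessment as unblinded.
5. State the reading rule for the primary outcome and for BP control, and use the mean of the two readings already planned.

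The cost is changed roles, some scheduling and one changed scoring rule; the number of readings stays the same. Rotating enumerators across arms would help but is optional. Section 3.4 places the arms in clearly separate locations, so rotation adds travel. Blinding at month 6 may remain imperfect, because Table 2 and section 3.6 put that assessment at the same time as the second intervention session at the pharmacy. The report should say so.
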